## Abstract

Social Prescribing (SP) involves linking individuals with mental illness to local health and welfare services to improve quality of life (QoL) and biopsychosocial wellbeing. SP programs address psychosocial wellbeing by linking individuals to group activities. Forest Therapy (FT) is a group nature walk with prescribed activities that promote mindfulness, relaxation, and shared experience. Improvements in psychological and physical wellbeing have been demonstrated in FT, but psychosocial impacts have not been widely investigated. This study will implement an SP FT intervention and assess the impacts on QoL and biopsychosocial wellbeing. Participants will include 140 community-living adults with mental illness at Sydney/Gold Coast, Australia. A stepped-wedge cluster randomised design will be used; each participant will complete a 10-week control period followed by a 10-week FT intervention. Weekly 90-min FT sessions will be conducted in groups of 6–10 in local nature reserves. Validated tools will measure self-report QoL and biopsychosocial wellbeing pre- and post-control and intervention periods, and 5-week follow-up. Blood pressure and heart rate will be measured pre- and post-FT sessions. Hypothesised outcomes include improvements in QoL and biopsychosocial wellbeing. This study is the first to assess SP FT, and may provide evidence for a novel, scalable mental illness intervention.

## 1. Introduction

The global prevalence of mental illness and substance use disorders is 15–20%, or over one billion people [1]. Similarly, the Australian prevalence of mental illness is 20%, and approximately half of Australians experience mental illness during their lifetime [2]. In Australia, Mental illness is the most common issue managed in General Practice (GP), being discussed in 62% of visits in 2018 [3] and placing increasing pressure on GP resources [4]. The most common course of treatment for mental illness is medication [4], however this approach only targets disease-specific neurological systems [5] and is not as effective as targeting the broad range of biological, psychological, and social factors implicated in mental illness [6].

An emerging approach to providing holistic care (treating this broad range of biopsychosocial factors) for individuals with mental illness is Social Prescribing (SP). SP involves care coordination and linkage programs where individuals with mental illness are referred to local community-based services [7]; these services can be public, private, or community-run volunteer services, and can target physical health (e.g., exercise groups, medication management), psychological health (e.g., disease-specific support groups, counselling), welfare (e.g., housing, employment services), and social support (e.g., group activities, befriending services). SP programs have been extensively implemented internationally [8]. For example a core component of the NHS England health policy is developing their SP programs which aims to increase the number of Link Workers (community care coordinators) by 1000 by 2021, and for 900,000 people to be involved in SP Programs by 2024 [9]. Similarly, SP has been implemented in Scandinavia [10], New Zealand [11], and The Netherlands[12]. SP programs have demonstrated improvements in physical wellbeing including self-reported health status [13], physical activity [14], energy, and fatigue [15,16]; psychological health such as QoL [17], depression, anxiety [18], health self-efficacy [16]; social participation [18], community participation [19], and perceived social support [13]. SP programs have also demonstrated decreased burden on the health system [14,20] including, decreased hospital admissions and GP visits [21], outpatient visits and allied health appointments [20], and prescription medication use [14].

Despite a plethora of international evidence a recent review by Bickerdike and colleagues concluded that many SP studies have a high risk-of-bias and that current evidence does not provide sufficient detail to demonstrate that SP improves participant wellbeing [22]. This review included 15 SP studies and concluded they were typically small scale, lacked comparative controls, lacked sufficient follow-up, and used non-validated tools [22]. However, given the number and variety of SP programs internationally, it is unlikely the 15 studies in this review are representative of SP. Additionally, the lack of robust evidence does not mean SP is ineffective [8]. SP interventions are necessarily translational and are implemented in a huge variety of health and community settings where formal control groups, large sample sizes, and long-term follow-ups are often not feasible due to pragmatic and financial limitations.

Regardless of this somewhat mixed evidence, SP is gaining momentum in other countries, for example Canada [23], USA [24], and Australia [8,25,26]. Thus far in Australia a small number of analogous programs have been implemented, for example the ‘How-R-U’ telephone support and referral program for elderly people discharged from hospital [27], ‘Reclink’ community-referral sport programs for at-risk youth [28], NGO Caritas’ faith-based community capacity-building programs [29], Feros Aged and Disability Care Services implementing diet, exercise, and socialisation activities [30], and most recently State and Federal government-funded programs in response to COVID-19 including the Victorian ‘Community Activation and Social Isolation Initiative’ which provides social support and welfare services via local government [31] and the ‘HeadtoHelp’ hub which provides all-ages access to mental health services [32].

However, Australia’s first holistic SP programs for individuals with mental illness and disabilities have only been active since 2016, primarily implemented by NGO Primary and Community Services (PCCS) [33,34]. These ongoing programs offer care-coordination and community referral to local public, private, and community-run health and welfare services, in addition to internal and external social activities (e.g., art classes, coffee groups). Participants in these programs have demonstrated improvements in QoL and self-assessed health status [34], biopsychosocial wellbeing, reduced health service use, and frequency and confidence in participating in social activities [33].

A social activity that may be appropriate in the context of SP due to its holistic approach to wellbeing is Forest Therapy (FT) [35]. FT is a type of Nature Therapy and is based on the Japanese practice of Shinrin-Yoku or ‘Forest Bathing’, the goal of which is a mindful submersion in nature [36]. FT involves gentle walks in nature with a prescribed series of activities such as breathing exercises, exploring textures by touching items (e.g., trees, grass), drawing a ‘sound map’, or collecting natural objects to make a group artwork [36]. Mindful exposure to nature is demonstrated to decrease physiological arousal and have a ‘calming’ effect [37]. This may be because, for example, overstimulation in urbanised cities leads to cognitive overload and attention fatigue [38], and that returning to the environment for which we are adapted is restorative [39].

Time spent in nature is demonstrated to improve psychological wellbeing [40,41], boost immune function, and promote healing [35]. For example, a 2017 review [41] assessed six international studies of healthy, unwell (alcohol dependence, hypertension, COPD), and elderly adults completing short (1 h) to long (9 day) FT sessions and concluded FT can improve hypertension, cardiac and pulmonary function, immune function, inflammation, oxidative stress, and stress hormones. The same review demonstrated psychological improvements including decreases in self-report stress, depression, and anxiety [41]. A recent (2020) review [42] of the impact of FT on mental illness assessed 20 international studies of healthy and unwell (depression, alcohol dependence, chronic pain, metabolic syndrome, stroke) adults completing short (15 min) to long (4 h) FT sessions and concluded FT improves symptoms of depression, anxiety, and anger [42]

Despite this extensive evidence regarding the physical and psychological impacts of FT, there is very little extant evidence regarding the benefits of FT on psychosocial wellbeing (e.g., social capital, loneliness, etc.). A recent review of seven SP nature-based activities concluded that these can promote socially connected and physically active communities [43]; however, the results of this review are difficult to generalise to adults with mental illness as the majority of participants were children and carer-child dyads [43]. Similarly, the results may not be applicable to FT as, while some activities included analogous activities such as visits to parks or local gardens, others included white water-rafting and visits to farmers markets [43]. Similarly, Nature Therapy more broadly has shown evidence of improving psychosocial wellbeing in the context of community gardens [44]; however, these are inherently cooperation-focussed, require infrastructure, and are only accessible to a local population.

In the context of FT, a small study (*n* = 9) in Seoul, South Korea investigated an “Urban Forest Therapy” intervention in a public park [45]. Participants attended four weekly two-hour sessions in the park, and reported “emotional bonding” with each other, in addition to improvements in self-confidence, self-worth, and self-esteem [45]. However, no further information was acquired so, although possible, it is not clear if these reported changes lead to sustained improvements in psychosocial wellbeing. Beyond these tangentially related studies, there is not a large body of literature regarding psychosocial wellbeing in FT. This may, in part at least, be because FT is generally not conducted in the context of SP and thus improvements in psychosocial functioning are not targeted or assessed.

This gap in the literature is important to investigate as the goal of SP is to holistically target wellbeing, and evidence that FT in the context of SP can improve QoL and biopsychosocial wellbeing (particularly psychosocial wellbeing) could elucidate a novel mental illness intervention. Importantly, this intervention has the potential for scalability as SP FT is affordable and flexible. SP programs can be implemented by community organisations [46], do not require specialised equipment or registered healthcare workers as activity guides, and while FT was developed in Forest biomes, it is transferable to other biomes and conditions [47]. This flexibility is particularly important in Australia, where this is large health disadvantage in regional and remote areas due to limited access to services ([AIHW [48]), and a plethora of varied landscapes. Similarly, affordability and flexibility could mean SP FT is potentially applicable and scalable on an international scale.

This study will be the first to implement and evaluate a SP FT program in Australia, and one of the first internationally. It will address some of the important limitations of previous studies [22] by including an adequate sample size, control group, clear follow-up assessments, and the use of validated tools. It will fill a gap in the research by elucidating the psychosocial impacts of SP FT in an Australian sample of adults with mental illness. It will contribute to existing practice by exploring a novel intervention in the context of SP. It will also provide initial evidence for a potential nationally scalable intervention for mental illness.

### 1.1. Aims

This study aims to assess the impact of a SP FT intervention on the QoL and biopsychosocial wellbeing of community-living adults with mental illness,

### 1.2. Hypotheses

It is hypothesised that, compared to control data (initial 10-week assessment period for all participants), over the course of the FT intervention participants will show improvements in QoL, and psychosocial, psychological, and physical wellbeing.

## 2. Methods

### 2.1. Design

This study will be a multi-site longitudinal stepped-wedge cluster randomised trial [49]. Each participant will complete an initial 10-week control period (with pre and post assessments) followed by the intervention in a group (cluster), thereby ‘acting as their own control’ [49]. Participants will be allocated to clusters in the order they enrol in the study, and commencement of each cluster will occur in random order [49]; randomisation will be conducted by author [name] using an online random permutation generator suggested by Suresh [50]. Randomisation information will be provided in writing to Link Workers at each site who will then liaise with the intervention clinician (author [name]) to commence clusters in the assigned order. Sites will complete the intervention sequentially.

Assessment timepoints include pre- and post-control period (assessments 1 and 2), pre- and post-intervention (assessments 3 and 4), and 5-weeks post intervention (assessment 5). Additional timepoints include pre (assessments A1–A10) and post (assessments B1–B10) all FT sessions. A flow diagram of study phases and assessment timepoints can be seen in Figure 1, below.

### 2.2. Participants

The study aims to recruit 140 adults with ongoing mental illness (mood and psychotic disorders), living in the community at the Gold Coast (expected *n* = 45) and in Sydney (expected *n* = 95). Participants will be care-coordination clients of PCCS, an NGO that has previously developed and implemented SP programs in Australia [33,34]. PCCS has a steady flow of new care-coordination clients (who are referred by their GP) and these will form the recruitment pool. Eligibility criteria include:

#### 2.2.1. Inclusion Criteria

Adult (aged 18+ years);Any sex i.e., male, female, or non-specified;Referred to PCCS by GP for SP program;Diagnosed with a mental illness (mood or psychotic disorder) *;Able to complete study questionnaires in English;Capable of providing informed consent.

* Classification of mental illnesses for inclusion are all those appearing in Section 2 of the Diagnostic and Statistical Manual of Mental Disorders, 5th Edition: DSM-5 [51], and diagnosed according. For example, neurodevelopmental disorders (autism spectrum), schizophrenia spectrum disorders, depressive and anxiety disorders, trauma-related disorders (post-traumatic stress), personality disorders, eating disorders, and substance dependence.

#### 2.2.2. Exclusion Criteria

Receiving inpatient care in the past 6 months;Current thoughts of harm to self or others;Cognitive deficit which prevents capacity to provide informed consent or to complete study questionnaires.

## 3. Recruitment and Informed Consent

Initial assessment and recruitment of participants will be conducted by PCCS ‘Link Workers’, who are experienced social workers or registered mental health nurses. Link Workers are responsible for the initial assessment, care-coordination and linkage, and ongoing management of PCCS client wellbeing. All new clients of PCCS will be assessed for eligibility during their initial intake assessment with their PCCS Link Worker. In addition to this eligibility assessment clients will receive their usual care from PCCS involving care-coordination and community referral to local public, private, and community-run biopsychosocial health and welfare services. Informed consent will be obtained by the Link Worker; they will provide clients a FT information brochure, the Participant Information Statement (PIS), and Participant Consent Form (PCF), allow sufficient time to read both, and answer all client questions. Link Workers will emphasise that clients are not required to participate in the research project to participate in the FT program, and they may withdraw their consent at any time. Clients will indicate consent by returning a signed PCF. All clients will also receive standard care from PCCS throughout the study.

## 4. Intervention

The intervention will include 10 weekly 90-min FT sessions in groups of 6–10. Sites include Gold Coast Baree-Badalla Reserve—public nature reserve, mangrove biome, 1.2 km pathed footpath [52]; and Sydney Ku-ring-gai Wildflower Garden—‘senses tracks’, 900 m, forest biome, flat unpaved track [53]. Sessions will be facilitated by a certified FT Guide [54] and accompanying PCCS health workers (mental health nurse/allied health) with a maximum ratio of 1 staff member to 3 participants. Intervention objectives and prescribed activates follow the guidebook of the International Nature and Forest Therapy Alliance [54].

### 4.1. Intervention Objectives

The objectives of the intervention are to:
Promote nature as a place of relaxation;Demonstrate mindfulness techniques;Develop a gratitude-based focus to enhance positive mood;Enhance wellbeing using a range of creative and sensory activities;Experience relaxing activities with others, increasing social connectedness through shared experiences;Develop an understanding of the importance of nature and local culture in a specific area.

### 4.2. Forest Therapy Sessions

Session structure is outlined below; an asterisk (*) indicates a session with a focus on social interactions.

Introduction to FT;Sensory tuning activity—designed to ground participants using a combination of breathing exercises and gentle physical movement;Introduction to the local environment—overview of ecological, historical, and cultural information;Creative and sensory activities designed to facilitate mindfulness, including:
a.Focusing on a specific nature point in the distance;b.Collecting fallen objects such as leaves and creating a collective artwork *;c.Creating a sound map of the area using paper/pens;d.Exploring textures in the natural environment by safely touching trees, grass, etc.
‘Sit spot’—sit quietly and observe nature in a safe and calm environment;Tea ceremony—drink tea and discuss favourite part of the experience *.

## 5. Data Collection

Assessments 1–5 will be conducted by participants’ Link Workers at PCCS offices. Additional assessments pre- and post-FT sessions will be conducted by PCCS staff at FT sites.

### 5.1. Data Matching and Confidentiality

Completed questionnaires will be non-identifiable, but for the purposes of longitudinal data-matching will include a participant-generated anonymous code based on the process of [55]. This will comprise:First letter of participant’s mother’s first name;Number of participant’s older brothers (living and deceased);Month participant was born;First letter of participant’s middle name (if none, use X).

### 5.2. Materials

#### 5.2.1. Demographics

Participant demographics will be collected at baseline (assessment 1), including age, sex, country of birth, first language, aboriginality, highest education, mental illness and disability diagnoses, employment status, living arrangements, and if they require assistance with Activities of Daily Living (ADLs).

The following tools will be used for assessments 1–5, i.e., pre- and post-control-period, pre- and post-intervention, and at 5-weeks post intervention (follow-up).

#### 5.2.2. Quality of Life

The World Health Organisation Brief assessment of QoL [56] assesses QoL over the previous 2 weeks. It is validated in adults with mental illness [57] and has good discriminant, content, and test-retest reliability [58]. Two overall items assess overall QoL and physical health, and four domains including social relationships, physical health, psychological health, and environment. Items are rated on a Likert scale from 1 (not at all/very poor) to 5 (completely/very good).

#### 5.2.3. Social Adjustment and ADLs

The Work and Social Adjustment Scale [59] assesses perceived impairment in functioning in five domains including employment, ADLs, social connection and support, and leisure activities, rated on from 0 (not at all [impaired]) to 8 (very severely [impaired]).

#### 5.2.4. Loneliness

The UCLA 3-item Loneliness Scale [60] assesses how frequently over the previous two-weeks participants have felt 1. left out, 2. isolated, and 3. lacking companionship, rated from 1 (never) to 4 (frequently).

#### 5.2.5. Depression

Patient Health Questionnaire-9 [61] assesses cognitive and behavioural depressive symptoms over the past two weeks, including mood, fatigue, appetite, and concentration, rated from 0 (not at all [experienced]) to 3 ([experienced] nearly every day).

#### 5.2.6. Anxiety

Generalised Anxiety Disorder Questionnaire [62] assesses the severity of anxiety symptoms over the past two weeks. Seven symptoms are rated according to frequency of interference with functioning from 0 (not at all) to 3 (nearly every day).

#### 5.2.7. Health Self-Efficacy

The Health Confidence Score [63] assesses health self-efficacy. Four items assess personal health knowledge, capacity to take action if needed, and perception of being included in health decisions. Items are rated from 1 (strongly agree) to 4 (strongly disagree).

#### 5.2.8. Health Service Utilisation

Health service utilisation will be assessed for the previous 4 weeks. This will include frequency of ambulance use, hospital visits, hospital admissions, and nights spent in hospital. It will also assess number of GP visits, number of allied health visits, and community health service utilisation (with details).

The following assessment tools will be used immediately prior-to and post-each FT session.

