#### 6.2.4. Health Service Utilisation

Frequency of ambulance use, hospital visits, hospital admissions, nights spent in hospital, GP visits, allied health, and community health service utilisation.

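### The GP visit that qualifies a person for entry can be counted as an outcome at assessment 1 only, which can bias the GP-visit comparison in a direction that depends on the contrast used

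*Protocol article*

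**What the plan says.** Section 2.2.1 lists as an inclusion criterion "Referred to PCCS by GP for SP program". Section 2.2 adds that "PCCS has a steady flow of new care-coordination clients (who are referred by their GP) and these will form the recruitment pool", and section 3 that "All new clients of PCCS will be assessed for eligibility during their initial intake assessment with their PCCS Link Worker".

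On the outcome, section 5.2.8 states "Health service utilisation will be assessed for the previous 4 weeks" and then "It will also assess number of GP visits". The schedule for this and the other questionnaires is given at the end of section 5.2.1: "The following tools will be used for assessments 1–5, i.e., pre- and post-control-period, pre- and post-intervention, and at 5-weeks post intervention (follow-up"). Section 6.2.4 makes the count a secondary outcome, within a list that ends "GP visits, allied health, and community health service utilisation".

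Sections 1.2 and 2.1 make the initial 10-week period, which opens with assessment 1, the comparator for FT. The Analysis paragraph of section 7 names a linear mixed model based on a cited guide to stepped-wedge trials. It does not say which contrast applies to GP visits.

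**The concern.** A person enters the trial because a GP saw and referred them. If that consultation lies within the recall window of assessment 1, the event that made the person eligible is also scored as an outcome event. This can happen in the first control window only, since the windows of assessments 2 to 5 contain no visit that entry requires. The count would then fall after assessment 1 whether or not FT does anything.

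The article's argument on concurrent care (section 9.3) is that ongoing assessment and referral are alike in the control and intervention periods. That does not cover the referral consultation, which precedes the control period and does not recur as a condition of entry.

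What is at stake is the reading of one secondary result. The introduction credits social prescribing with fewer GP visits and describes growing pressure on GP resources, so an apparent change in GP use would attract attention.

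**Working it through.** The article gives no rate, effect or sample size for GP visits, so there is no figure of its own to reproduce. The check is the expected bias when the true FT effect is zero.

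**Inputs from the article.** GP referral required (2.2.1); new clients approached at intake (2.2, 3); 4-week recall (5.2.8); assessments 1 to 5, called A1 to A5 here (2.1, 5.2.1); 140 participants in groups of 6 to 10 (2.2, 4).

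**Assumed.** p is the share of participants whose referral consultation falls in the 4 weeks before A1. It is not given and can lie anywhere from 0 to 1. Taking every such visit as extra to usual GP use makes p an upper bound on the excess at A1.

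**Step 1: simple contrasts.** Put the excess at (p, 0, 0, 0, 0) for A1 to A5.

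| Contrast | Bias | p = 0 | p = 0.25 | p = 0.5 | p = 1 |
|---|---|---|---|---|---|
| Mean of A4–A5 minus mean of A1–A3 | −p/3 | 0 | −0.08 | −0.17 | −0.33 |
| A4 minus mean of A1–A2 | −p/2 | 0 | −0.13 | −0.25 | −0.50 |
| (A4 − A3) − (A2 − A1) | +p | 0 | +0.25 | +0.50 | +1.00 |
| A4 − A2, or A4 − A3 | 0 | 0 | 0 | 0 | 0 |

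Units are visits per 4 weeks. A negative sign makes FT appear to reduce GP visits.

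**Step 2: the class of model named.** This was a generalised least squares fit with fixed calendar periods and a random cluster effect. It used:
- 14, 18 or 23 clusters (140/10 = 14; 140/6 ≈ 23);
- starts staggered by 5 or 10 weeks;
- a gap of 0, 5 or 10 weeks between A2 and A3;
- within-cluster correlation of 0.1, 0.5 or 0.8.

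That makes 3 × 2 × 3 × 3 = 54 scenarios, with stagger, gap and correlation all assumed. The bias ran from −0.31p to +0.35p. It was negative in 44 scenarios and positive in 10, of which 9 had correlation 0.8. If all clusters start on one date, the first period effect absorbs the excess and the bias is 0. With A1 left out, it was 0 in all 54.

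**Step 3: illustrative error rates.** Take A4 minus the mean of A1–A3 in 126 people, with within-person correlation 0.5 and no clustering:

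SE = SD × √(0.5 × (1 + 1/3)/126) = 0.073 for SD 1.0 and 0.109 for SD 1.5.

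With z = (p/3)/SE and a two-sided 5% test, the chance of a significant result is 12–21% at p = 0.25, 33–63% at p = 0.5 and from 86% to over 99% at p = 1. The SD, correlation and contrast are all assumed.

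**Step 4: cost of leaving A1 out.** Under equal correlations, the variance of A4 minus the mean of k control readings is proportional to 1 + 1/k. Going from k = 3 to k = 2 multiplies the SE by √(1.5/1.333) = 1.06. Section 9.3 gives a minimum of 25 weeks per participant, which is 10 + 10 + 5, so A2 and A3 may coincide. In that case k goes from 2 to 1 and the SE is multiplied by √(2/1.5) = 1.15.

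**The case against.** A reader might infer that the first control count is inflated as a matter of fact, that FT will therefore seem to reduce GP use, and that the false-positive risk is 12% to 99%. The documents do not support that reading.

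- **Timing.** The interval from referral to assessment 1 is not stated. Section 3 places the eligibility check at intake but dates neither intake nor assessment 1. If the interval always exceeds 4 weeks, p is 0 and there is no bias. This stands: the point is conditional.
- **Extra visits.** A GP may refer at a consultation that would have taken place anyway, in which case the excess is smaller than p. This stands: p is an upper bound.
- **Direction.** Section 1.2 speaks of improvement over the course of the intervention, which can be read as change and would work against FT. Section 7.1 refers to a difference between conditions after the intervention, which fits A4 versus A2 and has no bias. The mixed model can go either way. This stands: no single direction can be claimed.
- **Error rates.** They belong to a contrast the article does not specify, ignore clustering and start at p = 0.25. They are illustrative and are not properties of this plan.
- **Condensed article.** Item wording and contrasts for secondary outcomes may be settled in documents not shown. That limits the point but does not remove it. The article does fix the entry route, the recall window and the timing of assessment 1, and the problem comes from those three together.

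**Conclusion.** The concern holds in a conditional form. As described, the plan can count the qualifying GP visit in the first control window and in no other. If assessment 1 falls within 4 weeks of the referral for a share p of participants, that reading is raised by up to p visits. Any contrast that uses it can then be biased without an FT effect: by up to −p/3 or −p/2 for level comparisons, by up to +p for change versus change, and with either sign under the mixed model with staggered starts. Contrasts of assessment 4 with assessment 2 or 3 are unaffected.

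The size rests on p, which the article does not give, and on the referral visits being additional to usual use. The point concerns one count within one secondary domain. It does not touch the primary outcomes or the sample size. It is worth acting on because the remedy is very cheap and because a total count, once collected, does not allow the referral visit to be separated out.

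**What to change.** In section 5.2.8, word the assessment 1 item as GP visits other than the visit at which the person was referred to PCCS. This costs one phrase on one form and no precision. It removes the excess under every contrast, provided the referral visits were additional to usual use. Where a referral was made at a visit that would have happened anyway, the new wording drops a visit that belonged in the count, so a check is useful.

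As that check, or as a fallback if the form cannot be changed, leave the assessment 1 GP count out of the FT contrast and report it descriptively, with one sentence to that effect in section 6.2.4. The standard error for this outcome rises by about 6% if assessments 2 and 3 are separate readings and by about 15% if they coincide. The same sentence should name the contrast used for GP visits.
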